#### Cohort Study Assessment

The second will be a cohort study that will recruit pregnant women from a subset of study clusters and follow them from late in the third trimester of pregnancy until their child is 18 months old to examine the impact of the interventions on child growth at the individual level. This cohort study will allow us to examine subgroups for any modifying effects on the primary outcome, for example, the modifying effects of different levels of maternal education and household wealth on the impact of the intervention on the study outcomes. We will exclude women who are severely anemic (Hb<7 g/dL) or have chronic diseases such as tuberculosis, women who intend to migrate outside the subdistrict, infants born with a visible congenital defect, and multiple births (twins) from the cohort study.

### Program Impact Pathways

The Baduta interventions should operate through 4 intervention pathways, as shown in the program impact pathway illustrated in Figure 2. The first pathway is to improve nutritional status during pregnancy by improving the nutrient adequacy of diets through increased consumption of foods from animal sources and iron and folic acid supplements. The second is to improve the nutrient adequacy of infant and young child diets through improved dietary diversity. The third is to reduce infectious diseases and improve nutrient intake through adherence to exclusive breastfeeding in the first 6 months of life. The fourth is to reduce infectious diseases through improved water and sanitation practices.

**Figure 2 figure2:**
[figure not shown]
Impact pathways of the Baduta program interventions. IYC: infant and young child; TV: television.

### Process Evaluation

During the delivery of the interventions, we will also conduct a process evaluation to assess the intervention input, output, and outcomes related to the program impact pathway and responses of the target populations to the intervention and contextual factors affecting the intervention. We will integrate and align the process evaluation with process monitoring of the implementers of the interventions.

### Study Setting

We will perform the study in the Malang and Sidoarjo districts of East Java, Indonesia (see Multimedia Appendix 1—a map of East Java with the study districts marked), which had an estimated population of almost 2 million and 2.5 million in 2014, respectively. There are 350 villages in Sidoarjo and 390 villages in Malang. The population density of Sidoarjo (2891/km^2^) is almost 4 times the population density of Malang (780/km^2^) [27]. Sidoarjo is a peri-urban district, with 13% of households from urban areas, and most adults are employed as factory workers (36%) or providing public and private services (41%: trader, hotels, restaurant, and public institutions) [28]. Malang is a rural district, with 97% of households from rural areas, and most adults are employed as farmers (33%) or providing public and private services (34%: traders, hotels, restaurants, and public institutions) [29]. On the basis of the annual nutrition surveillance data from the Ministry of Health, there are 24% of children aged <5 years who are stunted in Sidoarjo and 31% in Malang. Approximately two-thirds of the children aged <5 years in Malang and a half in Sidoarjo attend integrated village health posts for weight monitoring [28,29].

There are 51 subdistricts available for the study (33 in Malang and 18 in Sidoarjo), with an average population of 86,000. On average, there are 1.3 community health centers in each subdistrict, and each covers a population of approximately 68,000 people. Within the catchment area of each community health center, there are, on average, 2.8 subcenters (*Pustu*) that cover 5 villages or about a population of 30,000. Primary health care outreach to the community uses monthly integrated village health posts organized by local female health volunteers who coordinate with the community health center staff and village midwives. Village midwives are trained midwives who reside in 1 village within the community health center catchment area and are part of the service network. The village midwives’ program is part of the government’s efforts to accelerate the improvement of community health, particularly concerning maternal and child health. The roles and responsibilities of village midwives include maternal and child health, family planning services, health promotion, and preventive services as well as early detection and initial treatment for maternal and child health conditions, including undernutrition.

### Cluster Selection and Design of Randomization

The unit of randomization for the study will be subdistricts, selected by the authors to prevent contamination as they will deliver the health system strengthening interventions through the subdistrict community health centers. It will only be feasible to randomize a limited number of subdistricts to the new interventions versus the standard programs. As we will be limited to 12 subdistrict clusters (6 intervention and 6 usual programs), it will not be possible to use simple randomization to allocate them randomly to the intervention or control groups.

We will use constrained randomization [30,31] to ensure a balanced distribution of covariates in the study treatment groups because of the limited number of subdistrict clusters in which it is feasible to conduct the study. There are 33 subdistricts in Malang and 18 subdistricts in Sidoarjo. We will exclude subdistricts with similar ongoing projects and small subdistricts (population <70,000), leaving 24 subdistricts eligible for the study.

We will conduct hierarchical cluster analysis on the 24 eligible subdistricts using data for each district from the 2011 Village Potential Statistics (Pendataan Potensi Desa/Kelurahan) data set and local health surveillance data. We will use indicators of household economic status, access to health care, and prevalence of undernutrition in children to identify a group of similar subdistricts. We will select a group of 12 of the most similar subdistricts and construct a list of the 924 possible combinations of 6 intervention subdistricts and 6 comparison subdistricts. We will perform the analyses for constrained randomization with SAS 9.2 (SAS Institute Inc) using an algorithm developed by Chaudhary and Moulton [32].

We will select combinations of intervention and comparison subdistricts with balanced covariates, as measured by a difference in (1) the average distance of the neighborhood to the closest community health care center with a cutoff value for balance <0.5 km, (2) the coverage of children weighted at village health posts with a cutoff value for balance <5%, (3) the prevalence of underweight children (weight-for-age less than –2 Z score from growth monitoring charts) with a cut off value for balance <2.5%, (4) the ratio of village health posts to the total population with a cutoff value for balance <1.6/10,000 population, and (5) the percentage of low-income families who have a local government Certificate of Disadvantage (Surat Miskin/Surat Keterangan Tidak Mampu) with a cutoff value for balance <5%. Using simple random sampling, we will select one of the balanced combinations of subdistricts for allocation of the study interventions.

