### Sampling Design and Sample Size

#### Sample Size

We estimated the targeted sample size for the study using the following assumptions: (1) in the 51 subdistricts in the Malang and Sidoarjo districts, there is a total population of approximately 4.4 million, with an average of approximately 86,000 per subdistrict; (2) assuming a crude birth rate of 17 per 1000 population per annum, 5% refuse, and 10% data losses, each subdistrict cluster would yield an average of 620 live births over 6 months; (3) an expected prevalence of stunting for children aged 0-23 months of 35% in the control clusters (based on unpublished survey data from Brebes, West Java, and Indonesian DHS data); (4) 80% power and 5% 2-sided alpha, and 1:1 ratio of interventions (subdistricts with and without the Baduta program) allocated; (5) design effect of 1.5 (lower than reported for the 2011 Indonesia DHS survey because of larger sized clusters); and (6) expected percentage point difference in the prevalence of stunting (0-23 months) between the intervention groups of 6% (35.0% in the control to 28.9% in the intervention group). (This is a relative reduction of 17%, which is lower than the 29% reduction in stunting reported in a recent meta-analysis [47] of education interventions to improve complementary feeding.)

A standard formula using established methods [48] for comparison of proportions to calculate the number of subjects required per intervention arm to test H_0_: *π*_0_=*π*_1_ is as follows:

where *z_α_*_/2_ and *z_β_* are standard normal distribution values for upper tail probabilities of *α*/2 and *β,* respectively, *π*_0_ is the proportion in control, *π*_1_ is the expected proportion in intervention, *m* is the number of individuals per cluster, and *ρ* is the intracluster correlation coefficient.

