Based on this calculation, the sample size required is 1392 mother-infant dyads from each group of 6 subdistrict clusters or approximately 232 mother-infant dyads per subdistrict cluster. We will round this up to 2800 mother-infant dyads per cross-sectional survey or 234 per subdistrict cluster. This sample size will provide 80% power assuming a Z score SD of 0.975 and 5% level of significance to detect a 0.15 Z score difference in height-for-age Z scores [49] between the intervention and the control groups in the end-line survey. Therefore, for the cross-sectional evaluation, we will select 2800 mothers of children aged 0-23 months and an additional 400 pregnant women from 12 subdistricts within the Sidoarjo and Malang districts.

For the cohort evaluation, to detect a difference in mean length-for-age Z score between the experimental and control groups at an end line of 0.35 Z score [50], assuming 80% power and 5% level of significance, with a design effect of 1.5 (see above), we will require a sample size of 272 mother-infant pairs in each of the intervention and comparison groups. Assuming a dropout rate of 25%, we need to recruit 680 mother-infant pairs (56-57 per subdistrict cluster).

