### Statistical Methods

The intention-to-treat principle will guide our data analysis, and we will include data from all participants even if they do not participate in all interventions. We will apply the guidelines of the Consolidated Standards of Reporting Trials statement for clustered randomized trials in the analysis and presentation of the results. We will conduct analyses at the woman or infant level adjusted for cluster randomization. Initially, we will assess the effectiveness of randomization by comparing potential confounding factors in both treatment groups. We will apply statistical tests with χ^2^ tests for categorical variables and an adjusted Wald test or the Fisher exact test for continuous variables to assess for any significant difference between treatment groups. *P* values <.05 will be considered to indicate a statistically significant difference between the groups. For selected dietary analyses of continuous variables, we will use the nonparametric rank order statistic, Somers’ D [51] (corresponding to rank-sum tests), as it can adjust for the cluster sampling design.

We will calculate frequency and percent distributions for categorical variables and mean and SD or median and interquartile range for continuous variables. We will characterize the dietary intake by age group, breastfeeding status (for infants aged 12-23 months), and intervention and comparison groups. We will generate medians and interquartile ranges for dietary intake distributions that are not normally distributed. We will plot the frequency distribution of IYCF practices by child age. We will also plot the frequency distribution of Z score indices (Z score curves) in 0.25 Z score intervals using a Lowes function to smooth the curves, and we will compare these distributions with the growth standard distribution. We will repeat these plots broken down by treatment groups.

For the cross-sectional evaluation, the primary analyses will compare the prevalence of stunting (low length-for-age<–2 Z score) and the 95% confidence intervals in each treatment group adjusted for clustering and any imbalanced baseline characteristics.

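### District is neither balanced in the randomisation nor a pre-specified model term, although the two districts' stated stunting levels differ by 7 points

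*Protocol article*

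**What the plan says.** The Study Setting section describes Malang as rural and Sidoarjo as peri-urban, with almost four times the population density. It reports that "there are 24% of children aged <5 years who are stunted in Sidoarjo and 31% in Malang". It also puts attendance at village health posts for weighing at about two-thirds in Malang and one half in Sidoarjo.

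The Sample Size section draws the clusters "from 12 subdistricts within the Sidoarjo and Malang districts". Cluster Selection and Design of Randomization takes the 12 most similar eligible subdistricts, lists all 924 six-v-six splits without separating the districts, and then restricts the list: "We will select combinations of intervention and comparison subdistricts with balanced covariates". The five criteria are distance to a health centre (<0.5 km), weighing coverage (<5%), underweight prevalence (<2.5%), health posts per population (<1.6/10,000) and low-income families (<5%).

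Under Statistical Methods, the primary survey analysis is "adjusted for clustering and any imbalanced baseline characteristics". The cohort model has treatment as a fixed effect, cluster as a random effect and a time-by-group interaction. District appears in neither.

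**The concern.** District is a known cluster-level factor with a stated difference in stunting, and it is the obvious stratum when clusters come from two districts. Two things can go wrong if it is in neither the design nor the model.

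- **Unequal split.** Part of the district difference is then carried into the comparison of the arms.
- **Equal split.** The arms are balanced, but the between-district variance stays in the cluster error term, so the standard error is wider than it need be.

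The stated adjustment rule is a weak safeguard because it depends on finding an imbalance. The article tests baseline differences at P<.05, and with 12 clusters a test that respects the clustering has little chance of flagging a cluster-level factor.

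**Working it through.** **Inputs from the article.** Target: "35.0% in the control to 28.9% in the intervention group", so 35.0 − 28.9 = 6.1 points. Error rates: "80% power and 5% 2-sided alpha, and 1:1 ratio of interventions". Design effect: "design effect of 1.5 (lower than reported for the 2011 Indonesia DHS survey because of larger sized clusters". District gap: 31 − 24 = 7 points. Result: "the sample size required is 1392 mother-infant dyads from each group of 6 subdistrict clusters", or 232 per cluster, rounded to 1400 per arm.

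**Reproducing the plan's figure.** The pooled two-proportion formula gives 917 per arm; 917 × 1.5 = 1375.5, within 1.2% of 1392.

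**Effect of an unequal split.** Shift = 7 × (Malang share of the intervention arm − Malang share of the control arm). The district mix is not stated; assume 6 + 6. The number of allocations with a Malang clusters in the intervention arm is C(6,a) × C(6,6−a).

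| Split of Malang clusters | Allocations of 924, before the five constraints | Shift (points) |
|---|---|---|
| 3:3 | 400 (43.3%) | 0 |
| 4:2 or 2:4 | 450 (48.7%) | 7 × 2/6 = 2.33 |
| 5:1 or 1:5 | 72 (7.8%) | 7 × 4/6 = 4.67 |
| 6:0 or 0:6 | 2 (0.2%) | 7 |

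2.33/6.1 = 38% of the target. With SE = √(1.5 × 2 × 0.35 × 0.65/1400) = 2.21 points, an unadjusted 2.33-point shift gives a two-sided type I error of about 18%, conditional on that split.

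**What the constraints remove.** The district gap in weighing attendance is about 16.7 points. If coverage followed district alone, a 4:2 split would differ by 16.7/3 = 5.6 points and fail the 5% cutoff. With an assumed within-district SD in coverage of 3 to 15 points, 29% to 50% of the allocations passing that cutoff are still 4:2 or worse; 5:1 or worse is at most about 4%. Only this cutoff was simulated.

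**Would the imbalance rule catch it?** A Fisher exact test on the clusters gives P = (450 + 72 + 2)/924 = 0.57 for 4:2 and (72 + 2)/924 = 0.08 for 5:1. Neither is below .05.

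**Precision.** A design effect of 1.5 implies ICC = 0.5/231 = 0.0022, and a between-cluster SD of √(0.0022 × 0.35 × 0.65) = 2.2 points. Two equal groups of clusters a distance g apart have an SD of g/2 from district alone, so district uses up the whole allowance at g = 2 × 2.2 = 4.4 points. Then:

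- ICC = (g/2)²/[p(1 − p)], with p = 0.35 or 0.275 (the mean of 24% and 31%)
- design effect = 1 + 231 × ICC
- power = Φ(0.061/√(design effect × 0.433/1400) − 1.96), where 0.433 = 0.35 × 0.65 + 0.289 × 0.711

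| g (points) | Design effect | Power |
|---|---|---|
| 7 | 2.24-2.42 | 64-61% |
| 5 | 1.64-1.72 | 77-75% |
| 3.5 | 1.31-1.36 | above 80% |

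Two simplifications pull in opposite directions. The formula treats district as ordinary random cluster variance. In an exactly 3:3 split only the estimated standard error is inflated, not the true spread. Power is then Φ((0.061 − 1.96 × SE)/0.0176), where 0.0176 = √(0.433/1400): about 66-70% at 7 points and 82-83% at 5. But these figures also assume no between-cluster variance other than district, and any such variance lowers them.

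**The case against.** Several counter-arguments are sound.

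- **The 7-point figure.** It is for children under 5 across whole districts. The endpoint is ages 0-23 months in 12 subdistricts chosen to be alike on undernutrition, economic status and access to care, so the gap among the study clusters may be smaller.
- **7 against 6.1.** A reader might infer from these numbers that district could account for the whole target effect. That needs complete separation of the arms by district, which is 2 of 924 splits on a 6 + 6 mix even before the cutoffs apply.
- **Change from baseline.** The Cross-Sectional Survey Assessment section says impact is judged by comparing change between arms. That cancels a district difference that is constant over time. It does not cancel differing district trends, and the Statistical Methods wording for the primary analysis is a comparison of prevalence. The cohort has no pre-intervention child measurement to subtract. Its field staff also work as one team per district, so differences between measurers would coincide with district.
- **Validity.** Clusters are randomised, so district imbalance is chance error, not bias in expectation. With a 3:3 split, leaving district out makes the test conservative, not invalid.
- **Analysis plan not shown.** The full covariate list may be set there. But the article fixes the randomisation criteria and states its own data-dependent adjustment rule, and that rule can be judged as written.

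**Conclusion.** The point holds in a limited form. District is absent from the balance criteria and from both models, and the stated rule would probably not bring it in.

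A realistic shift in an end-line survey comparison is about 1 to 2.3 points. The upper figure rests on a 6 + 6 mix, a 4:2 split and the full 7-point gap persisting; an odd number of Malang clusters split as evenly as possible gives 7/6 = 1.2 points. The article does not give the district split, so whether any imbalance occurred cannot be judged.

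It would be wrong to conclude that the stated power is not delivered. Power may fall below 80%, but only if the gap among the selected clusters is large enough. By the usual formula, and counting district as the only between-cluster variance, that threshold is about 4.4 points. The case for the district term does not depend on the exact size of the gap.

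**What to change.** State in Statistical Methods that district is a fixed effect in the primary survey model and in the cohort model, whether or not it looks imbalanced. Report the number of clusters from each district in each arm. The allocation is already done, so the remedy lies in the analysis.

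The cost is one sentence and one of about 10 cluster-level degrees of freedom (12 clusters less 2 arms). It is relatively more in the cohort if that uses fewer than 12 clusters. Adding all five balance covariates as well is not recommended: six extra terms would leave about 10 − 6 = 4 degrees of freedom, which is a real trade-off.

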### Hypotheses

#### Primary Hypothesis

A package of behavior change interventions and health system strengthening activities delivered to a rural population in East Java, Indonesia, over 18 months will improve women’s diet and iron supplementation in pregnancy, breastfeeding, and complementary feeding practices; promote hygienic food preparation; and promote use of clean drinking water. The interventions will reduce the prevalence of stunting (length-for-age Z score <-2 Z) in children aged 0 to 23 months by 6% (35% in the control group to 28.9% in the intervention group) as assessed in cross-sectional surveys, compared with areas with only the routine integrated village health post services.

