#### Cross-Sectional Survey Assessment

The first assessment approach will use repeated cross-sectional surveys of mothers of children aged 0-23 months and pregnant women at baseline before interventions commence and 2 years later at the end line, which is the best approach to assess the impact of the intervention on the stunting prevalence in the study population (population-level impact) [26]. In the cross-sectional surveys, we will collect information on socioeconomic and demographic characteristics, infant feeding practices including intentions of the mother to breastfeed and mother’s self-efficacy with breastfeeding, child morbidity reported by mother/caregiver, contact with the health system and exposure to the interventions, maternal and child anthropometry, and maternal and child hemoglobin. We will assess the impact by comparing the change in the prevalence of key indicators between the treatment groups in children aged <2 years and pregnant women.

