#### Anthropometry

Trained field workers will collect measurements of weight, recumbent length in infants, height in mothers, and mid-upper arm circumference in pregnant women using standard methods and equipment [39,40]. We will standardize the measurements of the anthropometry field workers using established methods before and during data collection [39]. In both the cross-sectional and cohort evaluations, 2 field workers will collect duplicate measurements of the weight and length of children aged <2 years. The field workers will take a third measurement if the difference between the first 2 measurements exceeds a predetermined allowable limit (see details below).

We will calculate the Z scores for infant length-for-age and weight-for-length using the 2006 WHO Child Growth Standard [41], and we will define stunting as a low length-for-age or <−2.00 SD from the reference mean and wasting as low weight-for-length or <−2.00 SD. We will collect mid-upper arm circumference from pregnant mothers and define it as low if <23 cm [42].

The field workers will collect all anthropometry data using in-field digital data capture on tablets with routines that immediately calculate Z scores and provide them with a warning about extreme values and the need for remeasurement to check for potential errors (ie, if first and second measurement differed by >0.7 cm for length and by >0.1 kg for weight). We will refer to children with very low weight-for-height (Z score<−3) to their local community health center for assessment and treatment of severe acute malnutrition.

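### None of the five allocation constraints is stunting, and the analysis adjusts only for imbalanced characteristics: baseline stunting should always be in the primary model

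*Protocol article*

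**What the plan says.** Cluster Selection and Design of Randomization explains the restriction by the small number of units: "As we will be limited to 12 subdistrict clusters (6 intervention and 6 usual programs". The plan is to "construct a list of the 924 possible combinations of 6 intervention subdistricts and 6 comparison subdistricts", keep those that meet five balance limits, and draw one at random.

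The limits concern distance ("the average distance of the neighborhood to the closest community health care center with a cutoff value for balance <0.5 km"), weighing coverage at health posts (5%), underweight ("the prevalence of underweight children (weight-for-age less than –2 Z score from growth monitoring charts", 2.5%), health posts per population (1.6 per 10,000) and poverty certificates (5%). Neither stunting nor length-for-age is among them. The same section uses the prevalence of child undernutrition, among other indicators, to choose the 12 most similar of 24 eligible subdistricts.

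The primary outcome of the cross-sectional evaluation is stunting at 0-23 months. Its baseline survey covers all 12 subdistricts and measures length; the surveys take place "at baseline before interventions commence and 2 years later at the end line". On analysis, Cross-Sectional Survey Assessment compares the change in prevalence between arms. Statistical Methods compares prevalence with adjustment for clustering and for those baseline characteristics that are imbalanced, after testing potential confounders with P<.05 as the criterion of significance.

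**The concern.** Restricted allocation is the plan's answer to having only 12 clusters, yet it does not act directly on the outcome by which the trial is judged. Its one nutritional criterion is a proxy. It is weight-for-age rather than length-for-age, and it comes from growth monitoring, a health-post service that not every child uses: "Approximately two-thirds of the children aged <5 years in Malang and a half in Sidoarjo attend integrated village health posts". The arms could meet all five limits and still differ in stunting at the start.

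The analysis is the second line of defence, but as worded it is conditional. A baseline stunting gap large enough to matter can fail to reach significance with 12 clusters, and baseline stunting would then stay out of the model. The change comparison always uses the baseline, but it does so inefficiently, because it carries the full sampling error of both surveys.

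**Working it through.** **Inputs from the article.** 12 subdistricts, 6 per arm; 924 allocations; stunting 35.0% v 28.9%, a target effect of 6.1 points; design effect 1.5; 232 children per subdistrict, rounded up to 234 (233 used below); under-5 stunting of 24% (Sidoarjo) and 31% (Malang).

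**The plan's own figures.** C(12,6) = 924, as stated. The standard two-proportion formula gives 917 per arm; 917 x 1.5 = 1,375.5, within about 1% of the stated 1,392.

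**Intracluster correlation.**
- Implied by the plan: (1.5 - 1)/(232 - 1) = 0.0022.
- Implied by the district gap, if the 12 subdistricts split evenly between districts (an assumption): 0.035^2/(0.275 x 0.725) = 0.006.
- 0.01 is added as an outer value; it has no source in the article.

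**Chance of a true starting gap above 3 points, about half the target effect.** Let B = rho x 0.35 x 0.65 be the between-subdistrict variance. The SD of the true gap under unrestricted 6 v 6 allocation is sqrt(B x 2/6).
- rho 0.0022: sqrt(B) = 2.24 points, SD of gap 1.29, probability 2%.
- rho 0.006: 3.69, 2.13, 16%.
- rho 0.01: 4.77, 2.75, about 27%.

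The five existing limits are treated here as unrelated to stunting, so these risks lean high.

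**Would a significance screen catch such a gap?** In simulation (200,000 draws per rho), a cluster-level t-test at P<.05 on observed baseline stunting misses about 73%, 81% and 85% of true gaps above 3 points at the three rhos.

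**Precision of three analyses of the end-line result.** Let W = 0.2275(1 - rho)/233 be the sampling variance of one subdistrict's prevalence, T = B + W, and r the correlation of subdistrict effects across the two years (assumed 0.8).
- Plain end-line contrast: variance T/3.
- Change comparison: 2(T - rB)/3.
- Baseline-adjusted: (T/3)(1 - R^2)(9/8), with R = rB/T. The factor 9/8 is the cost of estimating one slope from 12 clusters.

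At rho 0.0022, B = 5.005e-4, W = 9.742e-4 and T = 14.747e-4. The change SD is sqrt(2 x (14.747 - 4.004)e-4/3) = 2.68 points. R = 4.004/14.747 = 0.272, so the adjusted SD is sqrt(4.916e-4 x 0.926 x 1.125) = 2.26 points.

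| rho | End-line only | Change | Always adjusted |
|---|---|---|---|
| 0.0022 | 2.22 | 2.68 | 2.26 |
| 0.006 | 2.79 | 2.87 | 2.61 |
| 0.01 | 3.29 | 3.08 | 2.89 |

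Entries are SDs in percentage points. Formula and simulation agree to about 0.01; in the middle row the formulas give 2.88 and 2.62.

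**Sensitivity to r.** Adjustment beats the change comparison throughout r = 0.5 to 1: at r = 0.5, 2.86 to 2.32, 3.32 to 2.83 and 3.75 to 3.26; at r = 1, 2.55 to 2.21, 2.54 to 2.40 and 2.54 to 2.48. Against a plain end-line contrast at rho 0.0022, the penalty is 0.04 points at r = 0.8 and 0.10 at r = 0.5.

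**Adding a limit on the observed baseline stunting gap (<1 point).** About 24-35% of allocations meet it on its own. The chance of a true gap above 3 points falls to about 0.5%, 3% and 5%. With adjustment already in the model, the SD moves from 2.27 to 2.15, 2.61 to 2.47 and 2.88 to 2.73 (simulated), about 5-6%.

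**The case against.** The case for the plan has four parts.

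*Balancing on existing data is coherent.* The Limitations section says that census and surveillance information was used. The article gives stunting by district only, so underweight is a reasonable proxy at subdistrict level. This stands: nothing here is a contradiction.

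*The exposure is already reduced.* Selecting similar subdistricts partly on undernutrition narrows the spread before the draw, and both descriptions of the analysis use the baseline in some way. This stands in part. Selection makes subdistricts more alike but does not balance the arms, and conditional adjustment does not guarantee that baseline stunting enters the model. A reader might infer that any starting gap passes straight into the result. The documents do not support that, because they do not specify an unadjusted end-line contrast as the analysis.

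*The survey is a noisy balancing variable.* One subdistrict's estimate has a standard error of about 3.1 points, against a between-subdistrict SD of 2.2 at the plan's design effect. This stands, and it is why the sixth constraint adds little once the model adjusts.

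*Waiting for survey data may not be cheap.* Tablets give "in-field digital data capture on tablets with routines that immediately calculate Z scores", and a programme "delivered to a rural population in East Java, Indonesia, over 18 months" inside a two-year survey interval seems to leave up to six months. But recruitment of third-trimester women to the cohort began in February 2015, the month of the baseline survey, and follow-up to 18 months ended in December 2016, which puts births at about June 2015 or earlier. A later draw could let cohort births precede the programme. This stands.

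**Conclusion.** The point holds as a design weakness of modest size. Stunting is not constrained in the allocation, and its place in the primary model depends on an imbalance judgement that 12 clusters cannot make reliably. The risk of a true gap above 3 points is about 2% on the plan's own design effect. It reaches about 16% only if rho is 0.006, which rests on whole-district under-5 figures and an even district split that the article does not state.

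Two stronger readings are tempting and are not supported. The first is that the plan ignored stunting data it had in hand at allocation: the article places the survey before the interventions, not before the draw, and never gives the order of the two. The second is that the 2.5-point underweight tolerance, 41% of the 6.1-point target (2.5/6.1), lets that much bias into the result: it is a limit on underweight, not on stunting, and the relation between the two is not given.

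The precision figures assume normal subdistrict effects, equal cluster sizes, simple binomial sampling error within subdistricts and a two-year correlation of 0.8. The advantage over the change comparison holds for correlations from 0.5 to 1; the small penalty or gain against a plain end-line contrast depends on rho and on that correlation.

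**What to change.** In Statistical Methods, state that the primary stunting model for the end-line survey always includes subdistrict-level baseline stunting prevalence, whether or not it tests as imbalanced. Align Cross-Sectional Survey Assessment so that this model gives the primary estimate and the comparison of change is secondary. No new data are needed. The cost is one of 10 cluster degrees of freedom (the two-sided 5% t value rises from 2.228 to 2.262) and, at the lowest rho, 0.04 points of SD against a plain end-line contrast (0.10 if the correlation is 0.5).

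State also whether the allocation is drawn before or after the baseline survey. Only if it can follow the survey without delaying the programme for the cohort, add a sixth limit on the observed baseline stunting gap between arms, for example <1 to 1.5 points. Expect about 5-6% off the SD beyond adjustment; this is an upper bound, because the five existing limits may already capture part of it. The price is fewer acceptable allocations and a later start to preparation. The article reports both surveys as completed, so for this trial the model statement is the usable part, and the extra limit is a design-stage change.
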